
#### Exploratory outcomes

The effect of lithium carbonate on motor nerve function will be assessed as an exploratory objective. This procedure will only be performed at the UMC Utrecht (the Netherlands). A compound muscle action potential (CMAP) scan or electrophysiological muscle scan (MScan) is a non-invasive, well-tolerated electrophysiological method that provides information on the number of motor units, their size and axonal excitability [38–43]. The CMAP scan records the electrical muscle activity (CMAP) using surface electrodes. Approximately 500 transcutaneous nerve stimuli are delivered with decreasing stimulus currents ranging from supramaximal to subthreshold levels. The CMAP scan quantifies progression in muscles affected by motor neuron disease, and is related to functional decline and survival [38, 44–46] We will apply the CMAP scan in the lower arm (abductor pollicis brevis and abductor digiti minimi) and lower leg (extensor digitorum brevis and abductor hallucis, if the extensor digitorum brevis is paralytic, the tibialis anterior will be used), both left- and right-sided, at quarterly intervals during the first 12 months of follow-up.

### Participant timeline {13}

The participant timeline can be seen in (Table 1). Study medication administration and concomitant medication or medical procedures are continuously recorded. Adverse events are continuously monitored and documented. Serious adverse events are continuously monitored and reported.

**Table 1 Tab1:** Participant timeline

	Screening (−45 days)	Baseline	Days 7, 14, 21, 28, and 56	Month 3 (±7 days)	Month 6 (±7 days)	Month 9 (±7 days)	Month 12 (±7 days)	Month 15 (±7 days)	Month 18 (±7 days)	Month 21 (±7 days)	Month 24 (±7 days)
Informed consent	X										
Eligibility criteria review	X	X									
DNA sample (10 mL)^a^	X										
Randomization		X									
Demographic data and medical history	X	X									
Neurological examination		X					X				X
12-lead ECG		X		X			X				X
Dispense study medication		X		X	X	X	X	X	X	X	
Drug accountability and compliance				X	X	X	X	X	X	X	X
Vital signs and body weight		X		X	X	X	X	X	X	X	X
Blood sample (30 ml)		X		X	X	X	X	X	X	X	X
Blood sample (lithium level)			X	X	X	X	X	X	X	X	X
Urine sample (20 ml)		X		X	X	X	X	X	X	X	X
Pregnancy test^b^	*For WOCBP patients: at a monthly interval*										
Spirometry (SVC)	X	X		X	X	X	X	X	X	X	X
ALSFRS-R	X	X		X	X	X	X	X	X	X	X
Quality of life (VAS and EQ-5D)		X		X	X	X	X	X	X	X	X
LiSERS questionnaire			X	X							
King’s staging system		X		X	X	X	X	X	X	X	X
ECAS		X					X				X
ALS-FTD-Q		X					X				X
Optional: liquor biomarker sample		X			X		X				
Optional: CMAP scan^c^		X		X	X	X	X				
Survival data and ALS interventions^d^	X	X		X	X	X	X	X	X	X	X

^a^End-of-Study or early-termination visit

^b^Pregnancy tests can be performed by the patient themselves at home

^c^CMAP scan is only performed in the UMC Utrecht

^d^ALS interventions are gastrostomy, non-invasive ventilation, wheelchair use and tracheostomy

#### Sample size {14}

The sample size calculation for this event-driven trial is based on the primary efficacy end point death of any cause or respiratory insufficiency. The trial continues until the required number of events is reached or until 24 months after the last enrolled patient, whichever comes first. In the meta-analysis of lithium carbonate among patients homozygous for the C-allele at SNP rs12608932 in *UNC13A*, we found a crude hazard ratio (HR) of 0.43 and an adjusted HR of 0.30 (active vs. placebo) [8]. Due to the relatively small sample size of the meta-analysis (*n* = 46), we assumed a conservative hazard ratio of 0.50. With the use of a one-sided test at the 0.0250 significance level, the trial would have 80% power if it continued until 72 events occurred in the combined trial groups. We specified one pre-specified stopping rule for efficacy based on the Lan- DeMets procedure with O’Brien-Fleming alpha-spending function when 41 events occur (non-binding).

We used a simulation-based approach to estimate the event probability during follow-up and the required sample size. We assumed that 14.21% of the patients will be homozygous for the C-allele at SNP rs12608932 in *UNC13A*. With a planned maximum enrolment rate of 5–6 patients per month, enrolment of 171 patients (114 on active treatment and 57 on placebo) resulted in 72 events within 48 months since first enrolled patient for 99.5% of our simulated trials.

#### Recruitment {15}

Patients fulfilling the inclusion criteria, apart from homozygosity for the C-allele at SNP rs12608932 in *UNC13A* will be identified by their treating physicians and given the patient information verbally and handed the written information for review. Alternatively, patients can register themselves via the TRICALS website, after which patients will be approached with information regarding the trial [47]. Afterwards, a screening visit will be planned where informed consent will be taken and a blood sample for rs12608932 genotyping, or consent to extract the rs12608932 genotype if already available in other sources.

## Assignment of interventions: allocation

### Sequence generation {16a}

Randomization will be done using a centralized online response system (Research Online, Utrecht, the Netherlands, and Castor EDC, Amsterdam, The Netherlands), which assigns each randomized participant a unique identification number which will be used throughout the study. Randomization sequences in the study will be in random block sizes of 3–9, and stratified for trial site and risk category (high vs. low risk; low risk defined as a TRICALS risk profile of ≤ −4.5).

### Concealment mechanism {16b}

The allocation sequence is concealed by the centralized online response system.

### Implementation {16c}

Implementation is performed by research nurses and trial physicians.

## Assignment of interventions: blinding

### Who will be blinded {17a}

All staff, patients and personnel involved with the study will be masked to treatment, except site pharmacy personnel and the unblinded physicians. Furthermore, at least one sponsor safety employee will be unblinded in the case of serious safety events requiring unmasking. Information on lithium plasma levels is only accessible by the unblinded physicians. Lithium plasma levels will not be reported in (electronic) patient records.

### Procedure for unblinding if needed {17b}

In a medical emergency when identifying the patient’s treatment assignment may influence the patient’s clinical care, the Investigator may request the patient’s treatment assignment with the unblinded physician; 24-h emergency unblinding is available through the local pharmacy.

## Data collection and management

### Plans for assessment and collection of outcomes {18a}

During each clinical assessment patients will be asked about their current medication use and potential (serious) adverse events. All prescription drugs, over-the-counter medications, nutraceuticals, and herbal remedies will be recorded in the electronic case report form (eCRF). Additionally, ALS specific interventions such as gastrostomy placement, recommendation for wheelchair- and non-invasive ventilation (NIV) use will be recorded. Basic vital signs measurements (systolic and diastolic blood pressure, respiratory rate, heart rate and temperature) and body weight will be obtained. Details of all pregnancies in female patients and, female partners of male patients will be collected after the start of study drug and until conclusion of the pregnancy.

The ALSFRS-R questionnaire, the King’s- and ALS-MITOS staging will be filled out. Lung function is evaluated by using a non-invasive spirometer of the brand EasyOne to determine the Slow Vital Capacity (SVC), of which the highest of three attempts will be registered. During each follow-up period a venipuncture will be performed; approximately 20 ml will be obtained (4 tubes). All safety assessment will be evaluated locally. At baseline, Beta – HCG will be determined for female study patients. Additionally, patients will be asked to provide a urine sample. The urine sample (20 ml) will be used to screen for safety (dipstick or other method) and pregnancy.

Patients can optionally partake in lumbar punctures and CMAP scans. During the lumbar puncture, one vial (approximately 5 mL) of cerebrospinal fluid will be obtained at baseline, month 6 and month 12. Blood (serum and plasma), urine and CSF collected for biomarkers will be stored locally at −80 °C for at least the duration of the trial. CMAP scans will be made at baseline and months 3, 6, 9, and 12.

### Plans to promote participant retention and complete follow-up {18b}

As ALS progresses, patients may experience increasing difficulty to adhere to the nominal visiting schedule. To reduce discontinuations due to non-compliance, we provide an alternative monitoring option for debilitated patients, if allowed according to local laws and regulations. If, in the judgment of the principal investigator, the patient cannot reasonably be expected to travel to the clinic, the minimum data required for continued participation in the study (i.e., remain on the study medication) are laboratory tests, adverse event reporting and ALSFRS-R, all of which can be obtained remotely by a trial nurse, either during a home visit or by phone. Blood samples for safety assessments may be obtained by the patient’s general practitioner or any other local blood collection option that has been approved by the Sponsor. These data are to be obtained according to the nominal visit schedule until the patients withdraws, reaches the endpoint or the study completes, whichever comes first. If the patient becomes unfit for travel, this information will be documented in the source data. If no accommodations can be made for adequate safety monitoring, patients are withdrawn from study medication and the minimum requirement for follow-up will be assessment of survival data (i.e., living status or date of death).

### Data management {19}

A data management plan is available for this study. In brief, at screening the centralized online system will assign a unique patient identification number to each participant (Research Online, Utrecht, the Netherlands and Castor EDC, Amsterdam, The Netherlands). This identification number contains three letters to identify the site and three numbers to identify the patient (e.g., for the first patient in the UMC Utrecht; UMC-001). The identification number will be used for all eCRFs, laboratory tests and other administrative documents. Any patient identification numbers that are assigned will not be reused, even if the patient does not receive treatment (e.g., screening failures). All study data will be collected in pseudonymized form and stored in the online database of Research Online, located at the server of the UMC Utrecht, and Castor ED, located in the Netherlands. Appropriate technical and organizational measures will be implemented in order to ensure compliance with the GDPR. The trial nurse(s), research physician(s) and study monitors have access to this database. The data will be kept for 25 years.

### Confidentiality {27}

All data sheets are secured with a password and therefore only accessible for authorized individuals. The data will be saved on the server of the UMC Utrecht or the server of Castor. In case of inspection by health authorities (i.e., high rates of SUSARs) the study staff is obligated to provide the individual data. Patients are informed about this possibility by the patient information letter.

### Plans for collection, laboratory evaluation and storage of biological specimens for genetic or molecular analysis in this trial/future use {33}

Genetic testing will be performed for one genetic variant; the C-allele at SNP rs12608932. A blood sample of 10mL will be collected. DNA samples will be shipped to UMC Utrecht, Utrecht, the Netherlands (European samples) or Queensland Brain Institute, Brisbane, Australia (Australian samples)*.*

## Statistical methods

### Statistical methods for primary and secondary outcomes {20a}

The number and percentage of patients screened, randomized, receiving any study medication, completing the study, prematurely discontinuing treatment, and prematurely discontinuing from the study will be summarized by treatment arm and overall participation. Reason for premature discontinuation will be summarized.

#### Demography and baseline characteristics

Continuous variables are expressed as mean and standard deviation for normally distributed variables and median and range for non-normally distributed variables. Categorical variables will be presented as number of cases and percentage. Baseline characteristics will be compared between the placebo and intervention arm without significance testing. Demography will be summarized by allocation arm (active *vs.* placebo) and overall. Missing data will not be imputed unless otherwise specified. The following baseline variables will be calculated:Body mass index = weight (kg)/height^2^ (m)SVC _Predicted_ (L) = Predicted using GLI equation (Age, height, ethnicity, sex)Predicted %SVC = [SVC _Observed_ (L)/SVC _Predicted GLI2012_ (L)]*100% [48]Diagnostic delay (months) = [date diagnosis – date symptom onset]/365.25Symptom duration (months) = [date randomization – date symptom onset]/365.25ΔFRS = [ALSFRS-R _Baseline_ – 48]/symptom duration [49]TRICALS risk category: quintiles of the linear predictor based on the model described in Westeneng et al. [19]. Linear predictor is based on age, diagnostic delay, %SVC _Baseline_, ΔFRS, FTD, site of symptom onset, and El Escorial classification (see also {10} Eligibility criteria).Utrecht stage: Based on the ENCALS model, the median survival time from onset is predicted per patient (in months). Utrecht Stage is defined as symptom duration/median predicted survival time. Staging categories are I = 0–0.25; II = 0.25–0.5; III = 0.5–0.75; and IV = >0.75.

#### Analysis populations

*The efficacy population* will be used for the primary efficacy analysis. The efficacy population includes all randomized patients irrespective of follow-up or receiving the actual study medication (intention-to-treat). Patients will be analyzed according to their randomization assignment.*The safety population* will consist of all randomized patients who received at least one dose or portion of a dose of study medication. Patients will be analyzed according to the treatment they received.

#### General methods

The primary endpoint hypothesis tests will be 2-sided with a significance level of *α* = 0.05. Secondary endpoints will be considered exploratory, presented with 95% confidence intervals and without inferential statements. For each analysis, all available data (from first date of randomization to last follow-up) will be used.

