### Trial design {8}

This is a phase III, event-driven, double-blind, randomized, placebo-controlled, group sequential study to evaluate the efficacy of lithium carbonate in patients with ALS homozygous for the C-allele at SNP rs12608932. Assuming a prevalence of 14.21%, approximately 1200 patients will be genotyped in order to enroll 171 patients. Patients will be randomized to receive either lithium carbonate or placebo in a ratio of 2:1, resulting in 114 patients on lithium carbonate and 57 on placebo. To minimize the burden for patients on placebo, we defined an early stopping rule for both futility and superiority.

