### Interim analyses {21b}

We formalized one interim analysis with the ability to stop for superiority or futility, which will be conducted at 57% of the required number of events. The following stopping rules are defined (Table 2):

**Table 2 Tab2:** Pre-determined stopping rules

Analysis	% of events	Futility		Superiority	
		*Z*	*Beta-spend*	*Z*	*Alpha-spend*
**I**	57%	0.36	0.0370	2.60	0.0046
**II**	100%	1.99	0.1630	1.99	0.0204
**Total**			**0.20**		**0.025**

The pre-specified stopping rule for efficacy is be based on the Lan-DeMets procedure with O’Brien-Fleming alpha-spending function with an asymmetric two-sided group sequential design with 80% power and 2.5% type I error. Upper bound spending computations assumed that the trial will continue if the lower bound is crossed (i.e., non-binding). At the interim analysis, a standardized likelihood ratio test statistic is calculated and compared to the *Z*-values provided in the table above. As soon as the test-statistic falls outside either the futility or superiority boundary, the study may be stopped for either superiority or futility.

In case enrolment is slow or a stopping rule is crossed early, the trial is likely to be terminated before all 171 patients have been enrolled. If treatment is futile, the trial can be stopped on average after 28.0 months since first enrolled patient with an average sample size of 137 patients. In this scenario, the probability for individual patients to remain in the trial for 18 months or more is 11.3% and to complete 24 months is 1.8%.

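### The primary test is two-sided at 0.05 in General methods but one-sided at 0.025 with adjusted boundaries in the design, and General methods does not say its level is the overall one

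*Protocol article*

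**What the plan says.** Three sections of the protocol article describe the error rate of the primary test.

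- **General methods:** "The primary endpoint hypothesis tests will be 2-sided with a significance level of" 0.05. There is no mention of the interim look, of Table 2, or of whether the level applies overall or to each analysis.
- **Sample size {14}:** "With the use of a one-sided test at the 0.0250 significance level, the trial would have 80% power if it continued until 72 events occurred". The assumed hazard ratio is 0.50 and allocation is 2:1.
- **Interim analyses {21b}:** the boundaries belong to an "asymmetric two-sided group sequential design with 80% power and 2.5% type I error". Table 2 gives superiority Z 2.60 (alpha 0.0046) at 57% of events and Z 1.99 (alpha 0.0204) at the end, in total 0.025. On the other side there is only a futility bound, 0.36 at the interim, described as non-binding.

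The section on the primary outcome names a likelihood ratio test and uses it at the interim as well. The interim section places a standardized form of that statistic on the Z scale for comparison with Table 2.

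**The concern.** The success criterion of a phase III trial with a single primary endpoint should have one reading before unblinding. Here the section that sets the general rule for the primary test gives a different sidedness from the sample size section and does not point to the adjusted boundaries. Two things are left open.

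- **The final critical value.** A test at nominal two-sided 0.05 rejects at 1.96, whereas Table 2 requires 1.99. A final Z of 1.97 could then be argued either way, after the result is known.
- **The harm direction.** A two-sided test can reject in favour of placebo. Table 2 has no such boundary, so a final Z of -2.1 would be significant under General methods and merely a failure to show superiority under Table 2.

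**Working it through.** **Inputs.** Hazard ratio 0.50, 72 events, 80% power, one-sided 0.025 (Sample size); 2:1 allocation (Trial design); interim at 41 of 72 events, superiority Z 2.60 then 1.99, futility 0.36 non-binding (Sample size and Interim analyses).

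**1. The plan's event number.** By Schoenfeld's formula, with allocation fractions 2/3 and 1/3:

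events = (1.960 + 0.842)² / [(2/9) × (ln 0.5)²] = 7.85 / 0.1068 = 73.5, so 74.

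The plan states 72, within 3%. At 72 events, power without an interim look is 79.2%. One-sided 0.025 and two-sided 0.05 both give 74 events, so the sidedness label alone does not alter the size of the trial.

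**2. The plan's final boundary.** Under the null, Z₁ and Z₂ are bivariate normal with correlation √(41/72) = 0.755. Solve for c in

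P(Z₁ > 2.60) + P(Z₁ ≤ 2.60, Z₂ > c) = 0.025.

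This gives c = 1.992, against 1.99 in Table 2. The final boundary is therefore reproduced from the printed interim boundary and a one-sided total of 0.025.

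**3. Type I error under the two readings** (futility bound ignored, because it is non-binding):

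| Interim, final | Interim part | Final part | One-sided total |
|---|---|---|---|
| 2.60, 1.99 | 0.0047 | 0.0204 | 0.0251 |
| 2.60, 1.96 | 0.0047 | 0.0221 | 0.0267 |

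The first total is 0.025 within rounding of the boundaries. The second exceeds it by 0.0267/0.025 - 1, about 7% in relative terms. If the futility rule were always followed, the second total would be 0.0262.

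**4. Width of the disputed zone.** The two-sided nominal p-value at Z = 1.99 is 2 × 0.0233 = 0.0466, so the zone runs from p = 0.0466 to 0.05. On the hazard ratio scale, the approximate standard error of the log hazard ratio at 72 events is 1/√(72 × 2/9) = 1/4. The observed hazard ratio needed is exp(-1.99/4) = 0.608 or exp(-1.96/4) = 0.613.

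**5. Power.** With drift 4 × ln 2 = 2.773, power is 78.7% with a final boundary of 1.99 and 79.5% with 1.96 (futility ignored).

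**6. Can 1.99 be written in as a fixed number?** The Lan-DeMets O'Brien-Fleming-type function named in the interim section gives, at t = 41/72, cumulative alpha 2 × [1 - Φ(2.241/√t)] = 0.0030. That corresponds to an interim Z of 2.75 and a final Z of 1.98. Table 2 has 0.0046, 2.60 and 1.99. Its spends instead match a cubic function of the information fraction: 0.025 × 0.57³ = 0.0046 and 0.20 × 0.57³ = 0.0370. The value 1.99 follows from the printed 2.60, but not from the named function.

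**The case against.** A reader might infer that the plan sets two rival success thresholds for the final analysis. The text does not go that far. General methods prints no critical value, and the only final superiority boundary in the document is 1.99. Its 0.05 can fairly be read as the overall level, which is 0.025 in the benefit direction and equals both the sample size assumption and the Table 2 total. On that reading Table 2 simply implements it. This objection stands: 1.96 arises only if 0.05 is taken as the nominal level of the final test, which the wording permits but does not state.

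A reader might also infer that 1.96 could apply at both looks, which would give a one-sided error of 0.040. Table 2 fixes 2.60 for the interim, so the document does not support that.

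Nor does the plan leave the likelihood ratio test wholly without direction. The interim section compares a standardized statistic with Z-values that have separate futility and superiority bounds, which implies a sign. What remains is that the sign is not stated and that the sentence concerns only the interim analysis.

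The objection does not remove the rest. Sidedness differs between Sample size and General methods under either reading, General methods does not say its level is overall, and no boundary exists for a rejection in the harm direction.

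**Conclusion.** The text is wrong as written, with small consequence. Read as the overall level, General methods conflicts with the design only on sidedness. Read literally as a nominal level at the final look, it raises one-sided type I error from 2.5% to about 2.67% and changes the conclusion only for a final Z between 1.96 and 1.99. Planned event number, interim rule and effect estimate are unaffected, and power differs by less than one percentage point between the two final boundaries.

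The figures assume one interim look at 41 of 72 events, the printed interim boundary of 2.60, a non-binding futility rule, and the usual normal approximation with independent increments. The hazard ratio cut-offs also use the approximate standard error for 2:1 allocation. The correction is worth making because it costs almost nothing and removes a dispute that could otherwise arise only after the result is known.

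**What to change.** State one sidedness in Sample size, General methods and Interim analyses: overall one-sided 0.025 for benefit. In Interim analyses, make clear that the term two-sided refers to the pair of efficacy and futility bounds. Replace the sentence in General methods with wording such as:

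> The primary hypothesis is tested for benefit at an overall one-sided level of 0.025 across the interim and final analyses. The final critical value is the group-sequential boundary (currently Z = 1.99 in Table 2, nominal two-sided p about 0.0466), recomputed from the spending function at the actual event counts. At both analyses the standardized likelihood ratio statistic carries the sign of the treatment effect.

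The named spending function and Table 2 must be reconciled first. Otherwise a recomputation with the named function would not return the printed boundaries, and 1.99 should not be fixed as a constant.

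The cost is a few sentences. The final threshold is slightly stricter than a nominal 0.05 test, though no stricter than Table 2 already requires. A formal rejection in favour of placebo is given up. If the sponsor wants one, a harm boundary has to be added to Table 2.
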